### 3. ABBREVIATIONS

|                 |                                                                                                                                                                                 |
|-----------------|---------------------------------------------------------------------------------------------------------------------------------------------------------------------------------|
| ACTH     | Adrenocorticotropic hormone- pituitary hormone which modulates cortisol                                                                                                         |
| Addi-QoL | Addison's disease specific Quality of Life Questionnaire- a subjective health questionnaire validated in adrenal insufficiency                                                  |
| AE       | Adverse event                                                                                                                                                                   |
| AI       | Adrenal insufficiency- Condition in which individuals are unable to synthesise steroid hormones such as cortisol, a stress hormone. Without treatment, this condition is fatal. |
| AR       | Adverse Reaction                                                                                                                                                                |
| BALP     | Bone specific Alkaline Phosphatase- a bone formation marker                                                                                                                     |
| BMI      | Body Mass Index                                                                                                                                                                 |
| BNP      | Brain Natriuretic Peptide a cardiac marker                                                                                                                                      |
| CBG      | Cortisol Binding Globulin- a protein which binds cortisol in the blood                                                                                                          |
| CI       | Chief Investigator                                                                                                                                                              |
| CK       | Creatine Kinase- a muscle enzyme used to indicate muscle damage                                                                                                                 |
| FBC      | Full Blood Count                                                                                                                                                                |
| GNCQ     | German National Cohort Questionnaire- a measurement tool for infection rates                                                                                                    |
| HbA1c    | Haemoglobin A1c- a diabetic marker                                                                                                                                              |
| HOMA-IR  | Homeostatic Model Assessment for Insulin Resistance- an indicator of insulin sensitivity                                                                                        |
| hs-CRP   | High sensitivity C-reactive Protein a cardiovascular risk marker                                                                                                                |
| ICHNT    | Imperial College Healthcare NHS Trust- Incorporates St Mary's Hospital, Hammersmith Hospital and Charing Cross Hospital                                                         |
| ICTU     | Imperial Clinical Trials Unit                                                                                                                                                   |
| IMP      | Investigational Medicinal Product                                                                                                                                               |
| ITT      | Intention To Treat                                                                                                                                                              |
| IQR      | Interquartile Range                                                                                                                                                             |
| LFT      | Liver Function Tests                                                                                                                                                            |
| MAR      | Missing At Random                                                                                                                                                               |
| NIHR     | National Institute of Health Research                                                                                                                                           |
| NTX      | N-Telopeptide Crosslinks- a bone reabsorption marker                                                                                                                            |

PRED-AID Study Statistical Analysis Plan (SAP)

|              |                                                                                                                                                          |
|--------------|----------------------------------------------------------------------------------------------------------------------------------------------------------|
| OC    | Osteocalcin- a bone formation marker                                                                                                                     |
| P1NP  | Type 1 Pro-collagen N-terminal peptide- a bone formation marker                                                                                          |
| PP    | Per Protocol                                                                                                                                             |
| PTH   | Parathyroid Hormone                                                                                                                                      |
| SAE   | Serious Adverse Event                                                                                                                                    |
| SAR   | Serious Adverse Reaction                                                                                                                                 |
| SD    | Standard Deviation                                                                                                                                       |
| SF-36 | Short Form Health Survey-36- a subjective health questionnaire                                                                                           |
| SS    | Safety Set- a population of all participants who have received at least one dose of the assigned intervention, defined for the purpose of describing AEs |
| SUSAR | Suspected Unexpected Adverse Reaction                                                                                                                    |
| TFT   | Thyroid Function tests                                                                                                                                   |

#### **4. INTRODUCTION/STUDY SUMMARY**

Steroid replacement therapy is vital for the health of patients with adrenal insufficiency (AI), who are unable to produce the natural stress hormone, cortisol. The objectives of steroid replacement therapy are to replace the body's physiological requirements for cortisol without over-replacement and consequent Cushing's syndrome. Equally, under-replacement presents the risk of patients experiencing potentially fatal Addisonian crises(1). Appropriately replacing a patient's steroid requirement is a significant challenge(2).

Hydrocortisone is used in the majority of patients with AI in the UK(3). However, hydrocortisone has a short duration of action, necessitating dosing 3 times a day(4). Low-dose prednisolone is an alternative to hydrocortisone which needs only once-daily. There have been no studies directly comparing low-dose prednisolone to hydrocortisone treatment.

Using a two-arm, two-period, double-blind randomised crossover study design, this study aims to compare the effects of two routine treatments of AI, low dose prednisolone and standard regimens of hydrocortisone. The primary outcome will be bone health. Secondary outcomes include: Cardiovascular risk, Glycaemic control, Infection rates and severity, Immunology profiles, Adverse events and Adverse Reactions, Wellbeing and Compliance

#### **5. STUDY OBJECTIVES**

##### **5.1 PRIMARY OBJECTIVE**

To evaluate and compare the safety and efficacy of low dose prednisolone and hydrocortisone treatments for the management of AI.

#### **6. DESIGN**

##### **6.1 STUDY DESIGN**

This study will be a phase 3, two-period, randomised cross-over, double-blind study with two treatment arms:

A) Participants given once daily low dose prednisolone (at 2-5 mg, determined by the serum level of prednisolone at 8 hours after a test dose) with placebo tablets at lunch and in the afternoon for four months (first period); followed by hydrocortisone three times daily (at their stable therapeutic regimen or the dose identified post-screening) for four months in the second period

B) Participants given hydrocortisone three times daily (at their stable therapeutic regimen or the dose identified post-screening) for four months (first period); followed by given once daily low dose prednisolone (at 2-5 mg, determined by the serum level of prednisolone at 8 hours after a test dose) with placebo tablets at lunch and in the afternoon for four months in the second period

PRED-AID Study Statistical Analysis Plan (SAP)

Participants will be randomly assigned to begin with either treatment arm. Each treatment period will be continued for 4 consecutive months. Participants will then undergo a washout period during which they will be returned to their baseline treatment for a period of 2 weeks, before starting on the alternate treatment arm. The aim is to assess the effect of each treatment arm on bone health, surrogate markers of cardiovascular risk, glycaemic control, infection rates, immunology profiles, patient wellbeing and compliance. A schematic of the Study Visits, timeline and study events to be undertaken can be found in Appendix 1.

## 6.2 TREATMENT ARMS

At randomisation, participants will be allocated to one of two treatment arms, to receive either prednisolone therapy first, or hydrocortisone therapy first:

- A) Prednisolone first: participants will receive four months of prednisolone and placebo tablets in the first Study Period and hydrocortisone in the second, four-month Study Period.
- B) Hydrocortisone first: participants will receive four months of hydrocortisone in the first Study Period and prednisolone with placebo tablets in the second, four-month Study Period.

The dose of the participant's usual regimen will be unchanged from their pre-study dose. The dose of the alternative medication to be used will be elucidated prior to each participant's randomisation on the study.

## 6.3 STUDY POPULATION

The study population is patients with either primary (affecting the adrenal glands) or secondary (affecting the pituitary gland) AI, who require cortisol replacement treatment using prednisolone, hydrocortisone or other glucocorticoid.

## 6.4 INCLUSION CRITERIA

- Aged 18 – 70 years
- Male or female
- Diagnosed with AI for over 6 months according to standard diagnostic criteria
- Established on stable HC replacement or prednisolone replacement, dose not altered for at least 3 months
- Established on a stable dose of Fludrocortisone, if taking, dose not altered for at least 3 months
- Participants taking other hormone replacements (e.g. levothyroxine, testosterone or growth hormone in secondary adrenal insufficiency) are accepted providing that their replacement doses have not altered for at least 3 months
- Participants who are otherwise healthy enough to participate, as determined by pre-study medical history and physical examination.

PRED-AID Study Statistical Analysis Plan (SAP)

- Participants who are able and willing to give written informed consent to participate in the study.

## 6.5 EXCLUSION CRITERIA

- Participants with a diagnosis of Type 1 or Type 2 diabetes mellitus.
- Unable to give informed consent.
- Taking supplements or herbal medications that the participant is unwilling or unable to stop prior to and during the study period e.g. St John's Wort (may decrease prednisolone levels), Cat's claw, Echinacea (immunomodulatory properties).
- Currently taking medications that alter CYP3A4 metabolism of glucocorticoids that the participant is unwilling or unable to stop prior to and during the study period e.g. phenytoin, phenobarbital, rifampicin, rifabutin, carbamazepine, primidone, aminoglutethimide, itraconazole, ketoconazole, ciclosporin or ritonavir.
- Pregnancy, taking the combined oral contraceptive pill, or oral oestrogen replacement therapy due to the effects on cortisol binding globulin levels and determination of prednisolone levels. Transdermal oestrogen replacement is permitted.
- Diagnosis of congenital adrenal hyperplasia, untreated

## 6.6 BLINDING

This is a double-blind study. To achieve sufficient blinding, patients will receive an individual tablet specially made for this study to be taken at their usual dosing times. Whilst taking hydrocortisone, patients will receive a hydrocortisone tablet in the morning, at noon, and in the afternoon, at their appropriate respective doses. When on prednisolone, patients will receive a single prednisolone tablet in the morning, at the appropriate dose. They will then receive placebo tablets at noon and in the afternoon.

In the case of a medical emergency or in the event of a serious medical condition, when knowledge of treatment allocation is essential for the clinical management or welfare of the participant, an investigator or other physician managing the subject may decide to unblind that subject's treatment code.

## 6.7 SAMPLE SIZE

The intention is to recruit 55 participants, allowing for a 20% drop-out rate. With 44 completers analysed there is a minimum of 90% power to detect a 1.5 µg/L effect on osteocalcin with a two-sided test at the 5% level of significance, assuming an estimate of the SD at a single timepoint of 3.0 (5). This assumes cautiously that the correlation between the repeated measurements within patients across the two periods is 0.5, whereas a previous crossover trial(6) showed a correlation of 0.8.

Following a pilot study to elucidate a reference range for osteocalcin in healthy volunteers and patients with AI, it has been shown that individuals can demonstrate reductions of up to 2.4 µg/L in the short

PRED-AID Study Statistical Analysis Plan (SAP)

term after changes in their steroid replacement regimen. It is anticipated that that larger changes in osteocalcin will be seen when patients continue on their new regimens for a longer duration.

## 6.8 SCHEDULE OF TIME AND EVENTS

Pre-randomisation events are discussed in detail in the study protocol. The study will last 9 months for each participant. This will involve taking the first randomised treatment for 4 months in Study Period 1, followed by a 2-week washout period where patients return to their baseline therapy, and finally Study Period 2. Study Period 2 will also be a 4-month period in which the patient will take the alternative treatment to that used in Period 1.

There will be 3 planned study visits, and 4 scheduled telephone consultations during each Study Period (total of 6 study visits and 8 telephone consults over both periods). The study visits will be completed on Day 1 and Day 30 in the first month, and the final study visit of each treatment arm on Day 120. Telephone consultations will be on Days 8 and 15 in the first month, followed by further monthly consults on Day 60 and Day 90. Please refer to Appendix 1 for a schematic of the time and events on each study visit.

For each study visits, participants will be asked to attend the Clinical Research Facility at the Hammersmith Hospital at 0800h having fasted from 2200h the night before (permitting small sips of water only) and having taken their first steroid tablet of the day at least 2 hours prior. On arrival, observations including heart rate, blood pressure, weight and waist-hip circumferences will be recorded. Urine will be collected for measurement of additional bone markers. The urine will also be subjected to a pregnancy test in participants of child bearing potential. Routine safety blood tests, and immunological blood samples will be collected during each visit. Bone markers and glycaemic markers will also be measured. Participants will be asked to report any symptoms and to complete the SF-36, Addi-QoL and GNCQ questionnaires during each visit.

On the first day of each study period and during visit 1 (visit 4 in the second period), participants will take their usual baseline steroid replacement therapy. Participants will commence the blinded study medication from Day 2 until Day 120 (visit 3).

At the end of each study period, participants will be asked to return their remaining tablets, which will be used to gauge compliance.

## 6.9 Randomisation

Randomisation will be managed through the Oracle InForm data capture system. This is a validated GCP-compliant data capture and management system. The allocation to study arm will be based on the original randomisation list populated and held by an independent statistician at the ICTU, which will be available for reference and back-up if the InForm database is unavailable.

Participant demographic data will be uploaded to the InForm system at enrolment, when they will be assigned a Study ID. Participants will be randomised to a study arm, receiving a Study Drug ID based on their blocking factor. The Imperial pharmacy will be made aware of the allocation and will dispense the appropriate blinded study medication and specified placebo at the patient's individual dose, for the relevant study period.

PRED-AID Study Statistical Analysis Plan (SAP)

Participants will be randomised in this study to either: (A) having prednisolone first or; (B) having hydrocortisone, using stratified blocked randomisation. Randomisation will be blocked for type of AI (primary vs secondary) to minimise heterogeneity. Given stratification for type of AI, all analyses will be adjusted for type of AI. Block size will vary randomly, ranging from 2 to 6.

## **7. POPULATIONS OF ANALYSIS SETS**

### **7.1 INTENTION-TO-TREAT/RANDOMISED POPULATION**

The main analysis will follow the intention-to-treat principle (ITT). All available primary and secondary outcomes from eligible participants who have been randomised will be analysed within the treatment group to which they were randomised for the associated period, regardless of treatment subsequently received.

### **7.2 PER PROTOCOL POPULATION**

A secondary analysis will be performed on the per protocol (PP) population. All primary and secondary outcomes from participants who have completed all study visits successfully without unblinding or significant protocol deviations/violations (including non-compliance with medication) will be analysed.

The significance of protocol deviations/violations will be assessed by the trial management group, and the final decision as to whether a participant should be excluded from the per protocol analysis will lie with the Chief Investigator (CI).

## **8. VARIABLES OF ANALYSIS**

### **8.1 PRIMARY EFFICACY VARIABLES**

To evaluate the effects of two routine treatments of AI, low dose prednisolone and standard regimens of hydrocortisone on:

- Bone health
  - assessed by measurement of change in total osteocalcin and undercarboxylated osteocalcin, bone formation markers, between Day 1 (pre-blinded treatment) and Day 120 (4 months post blinded treatment).

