### 3.1 STUDY OUTCOME MEASURES

#### Primary Outcome:

- Bone health
  - assessed by measurement of change in osteocalcin, a bone formation marker

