Although a washout period is incorporated into the design of the study to minimise carry-over effects, we will assess whether there is any evidence of a carry-over effect by fitting a separate linear mixed model which further includes the treatment by period interaction.

The continuous secondary outcomes will be analysed using the same modelling approach as specified for the primary outcome.

PRED-AID Study Statistical Analysis Plan (SAP)

All treatment effect estimates will be reported with 95% confidence intervals. A two-sided 5% level of significance will be used to assess the primary outcome. Statistical analysis will be conducted using SPSS or Stata.

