#### **9.5 PRIMARY EFFICACY ANALYSIS**

As this is a two-period two-treatment crossover trial, the treatment effect will be estimated using a multi-level repeated measures linear mixed effect model. The change from baseline osteocalcin will be the dependent variable, at 30 days and 120 days. The model will include participant as a random effect and fixed effects for treatment and period, type of AI (primary vs secondary), baseline osteocalcin, use of a bone sparing agent, and time point (Day 30 and Day 120). An unstructured correlation matrix will be used for the residuals. The estimated treatment effect at 120 day will be reported with a 95% confidence interval and corresponding p value. The main conclusion of the trial will be based on this analysis time point. We will also report the treatment effect at 30 days.

The analysis will include all available follow-up data. The model is likelihood based and missing data will be assumed to be missing-at-random (MAR), conditional on the observed values of other variables included in the analysis. If there are missing values for baseline measure of a clinical outcome, they will be replaced by the mean of the observed baseline values for all participants in all treatment arms (mean imputation). Sensitivity analyses will assess the validity of the MAR assumption and address the impact of missing data for all patients if required (see Section 9.8).

Model assumptions, including the normality of residuals and random effects distributions will be assessed. If any assumptions are poorly met, then an appropriate transformation of the outcome (e.g. log transformation) will be considered.

If the repeated measured mixed effects model including both 30 and 120 day outcomes fails to converge, treatment effects will be estimated using separate mixed linear regression models for each follow-up time point, which include participant as a random effect and fixed effects for treatment and period, type of AI (primary vs secondary), baseline osteocalcin and use of a bone sparing agent. An unstructured correlation matrix will be used for the residuals.

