| 09:15                                                               | SHS surveys/GNCO                                                           |                                           |                                             |                                              | SHS surveys/GNCO                                                            |                                              |                                              | SHS surveys/GNCO                                                            |                                                         |

**AE:** Adverse Event; **SHS:** Subjective Health Status (including the short form health survey (SF-36) and AddiQoL); **GNCQ:** German National Cohort Questionnaire; **Blood profile 1:** fasting renal, bone and lipid profiles, bicarbonate, full blood count (FBC), glucose, insulin, fructosamine, HbA1c, creatine kinase (CK), Adrenocorticotrophic Hormone (ACTH), cortisol binding globulin (CBG), parathyroid hormone (PTH), vitamin D, bone-specific alkaline phosphatase (BALP), osteocalcin (OC), procollagen type 1 N-terminal propeptide (P1NP); **hs-CRP:** hs-CRP; **hs-Troponin I:** BNP assessment of soluble immunological antigens and assessment of white cell populations.

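### SAP 8.1 lists two osteocalcin measures as primary, but the protocol, sample size, 5% level and primary model cover one unspecified osteocalcin, and no rule says which carries the conclusion

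*Combined protocol and SAP*

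**What the plan says.** The relevant statements are these.

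- **SAP 8.1** puts two measures under the primary heading: bone health is "assessed by measurement of change in total osteocalcin and undercarboxylated osteocalcin, bone formation markers, between Day 1 (pre-blinded treatment) and Day 120". They are joined without ranking.
- **Protocol 3.1** has one primary outcome, bone health "assessed by measurement of change in osteocalcin, a bone formation marker". The form is not named.
- **SAP 6.7** (and protocol sections 3 and 9) sizes the trial on one effect, 1.5 µg/L, and one SD, 3.0, for "osteocalcin with a two-sided test at the 5% level of significance".
- **SAP 9.1** sets one threshold: "A two-sided 5% level of significance will be used to assess the primary outcome".
- **SAP 9.5** specifies one model: "The change from baseline osteocalcin will be the dependent variable, at 30 days and 120 days". It reports the Day 120 effect with a confidence interval and p value, and adds: "The main conclusion of the trial will be based on this analysis time point". Day 30 is therefore not a further primary test.
- **SAP Appendix 1** has a single generic osteocalcin entry in the blood profile.

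Undercarboxylated osteocalcin appears nowhere in either document except SAP 8.1. It is not among the secondary bone markers in SAP 8.2 or 9.6.1. No section gives a hierarchy, an alpha split, or a rule on whether one or both measures must show an effect.

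**The concern.** The primary variable decides what the trial concludes, and here the SAP differs from the protocol and from its own analysis section. An analyst who follows SAP 8.1 fits the SAP 9.5 model twice and obtains two Day 120 p values, each compared with 5%. An analyst who follows SAP 9.5 fits it once and has to decide which form is meant. If that decision comes after the results are visible, or if either result may be reported as the primary finding, the error rate for the primary conclusion is above the stated 5%. If instead both forms must show an effect, the error rate holds, but the power calculation, which is for one measure, no longer describes the trial.

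**Working it through.** **Inputs from SAP 6.7:** effect 1.5 µg/L; SD at one time point 3.0; within-patient correlation across periods 0.5 (described there as cautious, with 0.8 cited from an earlier crossover trial); 44 completers; 20% drop-out; two-sided 5%.

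**Inputs not in the documents, so assumed:** the correlation between the two test statistics, and the effect and SD of undercarboxylated osteocalcin. For power, the second marker is given the same standardised effect as the first.

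**1. The plan's own figure.**
- SD of the within-patient difference = 3.0 × √(2 × (1 − 0.5)) = 3.0.
- Noncentrality = 1.5 / (3.0/√44) = 3.317.
- Power by the noncentral t distribution = 90.0% (with 43 or 42 degrees of freedom). By normal approximation, Φ(3.317 − 1.960) = 91.3%.
- Recruitment = 44/0.8 = 55.

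The stated 90%, 44 and 55 are reproduced for one osteocalcin.

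**2. Either form suffices, each tested at 5%.** For independent tests the chance of at least one false positive is 1 − 0.95² = 9.75%. For correlated statistics it is one minus the bivariate normal probability that both lie within ±1.960:

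| Correlation between the two test statistics (assumed) | Type I error |
|---|---|
| 0 | 9.75% |
| 0.5 | 9.1% |
| 0.7 | 8.3% |
| 0.8 | 7.8% |
| 0.9 | 7.0% |
| 0.95 | 6.5% |
| 1 | 5% |

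The same figures apply if one form is reported but is picked because it was significant.

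**3. Both forms required, each at 5%.** The type I error does not exceed 5%. Joint power with 44 completers (normal approximation, within-patient correlation 0.5) is 83.3% for independent statistics, 85.2% at correlation 0.5, 88.4% at 0.9 and 89.3% at 0.95. The figure to compare with is 91.3% for one marker, on the same approximation.

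This loss depends on the within-patient correlation. At 0.6 the SD of the difference is 3.0 × √0.8 = 2.683 and the noncentrality is 1.5/(2.683/√44) = 3.708. Single-marker power is then Φ(1.748) = 96.0%, and joint power for independent statistics is 0.960² ≈ 92.1%. At 0.8 it is 99.9%.

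**4. Both kept as alternatives with alpha split 0.025 each.** With 44 completers at within-patient correlation 0.5, power per marker is 83.5% to 83.6% by the t distribution (85.9% by normal approximation). Restoring 90% takes 53 completers, and 53/0.8 = 66.25, so 67 recruited. At a within-patient correlation of 0.8, power at 0.025 is 99.8% and 44 completers are enough.

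**5. One form named as the only primary.** Nothing changes from step 1: 5% alpha, 44 completers, 55 recruited, 90.0% power.

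**The case against.** The best defence is that SAP 9.5 is the operative section and describes one dependent variable, one model and one Day 120 effect with its p value. SAP 9.1 refers to a single primary outcome, and the SAP's contents list gives the 8.1 title in the singular. On that reading there are not two tests at 5%; the plan has simply not said which form it means. This is a fair reading, and it is why the inflation can only be stated conditionally. It does not remove the problem, because SAP 8.1 names two measures and 9.5 does not choose between them.

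A reader might infer that the primary error rate is already uncontrolled at nearly 10%. The documents do not support that. They do not say that either form is sufficient, and independence is hard to credit for a total measure and one form of the same analyte.

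A reader might also infer that requiring both forms necessarily breaks the 90% power. That holds only at the within-patient correlation of 0.5 and under the equal-effect assumption. At 0.6 or more, joint power exceeds 90%.

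Two further points stand. Neither the protocol nor the sample size says total osteocalcin, so that choice cannot be presented as already made. The single osteocalcin entry in the blood profile is weak evidence that only one form is measured, because the list is not exhaustive: liver function tests are a planned outcome and are not named in it.

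Finally, protocol 1.2 expects equivalence, so a significant difference is not plainly the favourable result. The trial is nevertheless powered and tested for a difference, so the error rate of that test still matters.

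**Conclusion.** The inconsistency is certain from the text: SAP 8.1 names two primary measures, every other primary specification covers one, and no rule connects them. Its consequence depends on a reading that the SAP leaves open.

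- Either form suffices, or the form is chosen after the data are seen: type I error of about 6.5% to 9.75% across assumed between-marker correlations from 0.95 down to 0.
- Both required: alpha controlled, joint power about 83% to 89% at within-patient correlation 0.5, with equal standardised effects assumed.
- One form intended: no multiplicity, but the primary variable is not identified.

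The sample size is sound for one osteocalcin. The point should be settled before unblinding because it concerns which measurement carries the main conclusion.

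**What to change.** In SAP 8.1 and 9.5, name one form of osteocalcin at Day 120 as the single primary variable, and use the same name in SAP 6.7 and protocol 3.1. Total osteocalcin is the natural choice, provided the sponsor confirms that it is the measure behind the SD of 3.0. Move undercarboxylated osteocalcin to the secondary bone markers in SAP 8.2 and 9.6.1. The design figures do not change.

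If the sponsor prefers to keep both as primary, the SAP should state one rule: a fixed sequence with its order, an alpha split, or a requirement that both show an effect. It should then restate the power to match, with a stated effect and SD for the undercarboxylated form.

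The preferred change costs only wording, made before any unblinded data are extracted; protocol section 9 already requires the steering committee to agree the SAP before then. Keeping both under an equal alpha split could cost 12 more recruits (67 − 55) at the design's within-patient correlation of 0.5.
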